### Trial treatment(s)/intervention

#### Group 1: Standard arthroscopic debridement (control)

The control group will be an arthroscopic debridement of the subacromial space with removal of inflamed tissue (bursectomy) and unstable remnants of the torn tendon, limited bone resection of the acromion, retention of the coracoacromial ligament and biceps tenotomy (if not already torn). The anaesthetic will be left to the choice of the anaesthetist; this may include general or local anaesthesia. Surgeons may use their normal surgical technique, within the confines described in a trial specific surgical guideline (available at the trial website or at request from Warwick CTU).

#### Group 2: Standard arthroscopic debridement plus insertion of InSpace Balloon (intervention)

Arthroscopic debridement, as described above, with insertion of the InSpace Balloon performed by subspecialty trained shoulder surgeons. The same arthroscopic debridement will be performed as described for the control group. If allocated to the balloon procedure, the company’s recommended surgical technique will be followed for sizing, insertion and deployment of the balloon, as documented in the surgical manual.

For both groups, fidelity will be assessed with an operative record form and arthroscopic photographs taken at the end of debridement and just before balloon inflation, and the number of physiotherapy visits for each participant will be documented in both arms.

### Rehabilitation

Postoperative rehabilitation for both groups will be blind to treatment allocation and will include standardised postoperative information, home exercises and the offer of a minimum of three face-to-face physiotherapy appointments. Additional physiotherapy will be at the discretion of the trial sites. A physiotherapy trial manual will be followed to standardise rehabilitation progression. All materials were developed through a process of collecting current National Health Service (NHS) protocols, manufacturer protocols, scoping the literature and expert consensus.

### Blinding

Treatment allocation will be blinded for both patients and assessors, only the surgical teams at the time of the operation will be aware of the allocation. Theatre staff are asked not to discuss the balloon and to communicate the allocation by using methods such as holding up a piece of paper on which the allocation is clearly written. If participants are awake, drapes are used to obscure the participant’s view and arthroscopic screens will be positioned in such a way that the patient is unable to see the procedure.

The incisions required for the two operations are similar and there is no external way in which the patients will be able to detect the presence or absence of the balloon, except for the size of the lateral portal. One of the incisions (the lateral portal) will need to be slightly larger to insert the balloon—1.5 cm as opposed to 1 cm. A 1.5 cm incision will be used for all participants, which is a very small change from standard care and is very unlikely to have a negative effect on any participant. Incisions will therefore be the same for both groups.

The operation note will be blinded to prevent accidental unblinding of the patient (eg, in the discharge information or during postoperative physiotherapy). A standard recommended operation note template will be given to all sites adjusted to fit their local operation note systems. The details of the operation related to the balloon will be recorded in a secure online form easily accessible to the surgeon.

Unblinding may very rarely be required in an emergency situation, such as an overnight admission for suspected postoperative infection. Unblinding will be performed only by NHS staff in an emergency situation, by using a predefined web-based system, from a link inserted in the operation note. A two-way secure verification process will be performed using email, and an access code will be emailed only to an active NHS email address. A full explanation of the clinical circumstances and the need for access to data will be requested by the trial team for audit and monitoring purposes from the person who performed the unblinding, and the principal investigator for the site will be informed. The system has been designed and tested by the WCTU programming team to ensure that it is both secure and fully functional.

Participants will be asked at the 12-month time point, after collection of the primary outcome, if they were aware of their allocation.

### End of trial

The trial will end when all participants have completed their 24-month follow-up, but the results will be published after the 12-month outcomes have been analysed, with a secondary report after collection of 24-month outcomes.

The trial may be stopped prematurely if: (1) mandated by the Ethics Committee; (2) there is an unexpected major safety concern; (3) following recommendations from the DMC or TSC, which may include meeting the adaptive design boundaries or (4) funding for the trial ceases

Once a decision to stop has been taken, those within a short waiting time to surgery may be randomised at the discretion of the DMC and TSC, but after that participants will be treated according to the judgement of their clinician.

### MRI substudy

Participants selected for inclusion in the MRI substudy will undergo two research MRI scans at 8 weeks and 6 months post-operatively. MRI scans were preferred to X-rays for this purpose as measures taken from X-rays would be prone to error, primarily due to variation in the angle between the shoulder joint and the beam of the X-ray. This will assess the mechanism of action of the balloon, when the balloons are likely to be still inflated (but when acute postoperative pain has subsided), and when they are likely to have fully deflated, to see if the proposed mechanism for ongoing improvement is maintained. Passive imaging alone will not be adequate to demonstrate the function of the balloon and imaging will also need to be performed when the deltoid muscle is active, producing a proximally directed force on the humerus.^53 54^

For this study, we have developed (and piloted) a novel dynamic approach to assessing the function of the rotator cuff using MRI imaging under a mild deltoid load, to specifically assess the mechanism of the balloon. A separate paper on the pilot study for the trial is in preparation and will describe these methods in more detail.

All participants will be eligible (unless they have a contraindication to MRI, or do not want to take part in the substudy), but the substudy will only be undertaken at a proportion of participating sites. The primary outcome will be the minimum acromiohumeral distance on the ‘deltoid-active’ coronal sequences at 6 months, a reliable and proven measure.^55–57^ The balloon is expected to have deflated by 6 months.^58^ Secondary measures will be acromiohumeral distance on passive images, and the change in acromio-humeral distance between active and passive images. The position of the balloon will be assessed to check for migration and consistency of placement relative to the acromion.

### Adverse events, adverse device effects, serious adverse device effects

Adverse events (AEs), serious AEs (SAEs), adverse device effects (ADE) and serious ADEs (SADE) will be defined using standard accepted criteria. An unanticipated SADE (USADE) is defined as an SADE which by its nature, incidence, severity or outcome has not been identified in the current version of the risk analysis report.

For the purposes of this trial, AEs will be recorded for any participant where it is thought there may be a relationship between the trial interventions or the condition being studied (in this case, any shoulder condition or related to the anaesthetic). These include device specific complications such as balloon migration, which will be recorded if it is identified by clinical teams from their normal practice.

All SAEs, SADEs and USADEs occurring from the time of randomisation until 12 months postrandomisation must be communicated to the sponsor within 24 hours of the research staff becoming aware of the event. Events will be followed up until the event has resolved or a final outcome has been reached.

Where participants have been lost to follow-up at or beyond the 12-month time point, and data on AEs can therefore not be recorded, the participants general practitioner (GP) will be contacted and a short form requesting any information or health record that could be an AE will be requested from the GP, as well as confirmation of the current contact details of the participant.

## Statistical analysis

### Power and sample size

The initial sample size calculations were based on the Constant Score. The target difference that was chosen for the Constant Score was 10 units, as has been widely used for other trials, and the SD was taken to be 20, giving a moderate standardised mean difference of 0.5.^17 23 59 60^ Anchor-based studies have estimated the target difference for the OSS as 6 and an SD of 12 has been observed in multiple studies, therefore, a moderate standardised mean difference of 0.5 remains appropriate.^41–43 60^

For a costly invasive procedure of this nature, a smaller standardised mean difference is unlikely to be considered worthwhile. For a power of 90% and a (two-sided) type I error rate of 5% a study with a conventional fixed design (ie, with no possibility of stopping early), assuming an approximate normal distribution for the score data, would require 170 participants.

In order to assess the design characteristics and estimate the required sample size for the planned adaptive design, we undertook a large simulation study (see Parsons *et al*
38). As we expect correlations between time points (based on Karthikeyan *et al)* and effect sizes to be equivalent between the Constant Score and Oxford Scores, these simulations remain valid, despite the change of primary outcome score.^41 60^ The simulations showed that an adaptive design that allowed the possibility of early stopping for efficacy and/or futility, was feasible for the START:REACTS study.

Based on an assumed modest correlation between 3-month, 6-month and 12-month OSSs equal to 0.5, and SD of 12 for both three and 6-month scores, the simulations for the selected adaptive design indicated that 188 participants would be sufficient to detect a 6 point difference in OSS between treatment arms with 90% power, and 5% (two-sided) type I error rate. Allowing for 15% lost to follow-up, while striving to keep this below 10%, gives a maximum study sample size of 221.

The sample size for the MRI substudy is based on the study by Gumina *et al*
55, where the minimum acromiohumeral distance had an SD of 1.72 mm. To observe a minimum important difference of 1.5 mm (larger than the minimum detectable change of 1.3 mm established elsewhere^61^) with an alpha of 0.05 at 80% power, assuming a lost to follow-up at 6 months of 20%, requires 56 participants for the MRI substudy.

### Statistical analysis plan

All data will be analysed and reported in accordance with the Consolidated Standards of Reporting Trials (CONSORT) guidelines.^62 63^ A detailed statistical analysis plan and a data sharing plan will be agreed with the DMC prior to any formal analyses being conducted.

Baseline data will be summarised to check comparability between treatment arms. Standard statistical summaries (eg, means and SD, dependent on data type) will be presented for the primary outcome measure and all secondary outcome measures.

The primary analysis will investigate differences in the OSS 12 months after surgery between the two treatment groups. It will be conducted on an intention-to-treat basis following the methods, test statistics and boundaries described by Parsons *et al*.^38^ To preserve the integrity of the study, the exact boundaries used for testing are given in the adaptive charter known only to the study team and independent DMC. Briefly, if the study recruits to target, the method set out by Parsons *et al*
38 will be used to calculate the boundaries and if the study stops early, testing will proceed using boundaries calculated by the deletion method for overrunning analysis, described by Whitehead, with clinical inferences following directly from widely used methods for unbiased estimates and confidence intervals in group sequential trials.^64–66^

The primary analysis will be augmented by calculating adjusted estimates of treatment group differences (with 95% CIs) for the OSS using a mixed-effects model. The mixed-effects model will include a random effect for the recruiting centre, and fixed effects for the variables of interest included in the minimisation algorithm, patient age, gender and size of tear. In addition, subject to the observed data, sensitivity analyses such as per-protocol analyses or multiple imputation will also be undertaken. If undertaken, all multiple imputation assumptions will be justified and reported. Estimates of efficacy for the other outcome measures will follow this approach to analysis.

Prespecified subgroup analyses will be undertaken to assess whether there is evidence that the intervention effect differs with respect to:

The size of the rotator cuff tear as measured at the start of surgery, defined as large or massive cuff tear (≥3 cm) or moderate to small (<3 cm).Gender.Age (>70 or <70).

These have been chosen as they are either important to the function of the intervention (cuff tear size) or to interpretation (gender and age). The subgroup analyses will follow the methods described for the mixed effects model of the OSS above, with additional interaction terms incorporated into the mixed-effects regression model to assess the level of support for these hypotheses. The study is not powered to formally test these hypotheses, so they will be reported as exploratory analyses only, and as subsidiary to the analysis reporting the main effects of the intervention in the full study population.^67^

Interim analyses will only be undertaken following the principles laid out by Parsons *et al*.^38^ Details of the timings or settings for the interim analyses will be treated as confidential information, so as not to prejudice the outcome of the trial based on the decision to stop the study or proceed, but will be recorded in the DMC minutes and on date-stamped internal documents. If a decision to stop the study early is made (for reasons other than safety), it will not be communicated outside of the DMC closed meeting whether this is for efficacy or futility.

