### Randomisation

Participants are randomly allocated on a 1:1 basis to the two treatment groups via a central computer-based randomisation system provided by Warwick Clinical Trials Unit (WCTU) independent of the study team. A minimisation algorithm is used to determine participant allocation, using site, gender, age group (<70 years and ≥70 years) and cuff tear size (as assessed by the operating surgeon, ≥3 cm or <3 cm) as factors, with a random element included to provide a 70% chance that the participant will receive the treatment that minimises the imbalance, to ensure unpredictability.

Randomisation will be performed by theatre staff, after the intraoperative findings have been checked (including cuff tear size) and eligibility is confirmed. Staff use an online system in a separate room to maintain blinding, with a 24-hour back-up automated telephone system available.

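### The sequential primary test and estimate appear to be unadjusted for the minimisation factors and for baseline OSS, which makes the test somewhat conservative and less precise than it could be

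*Protocol article*

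**What the plan says.** Under Randomisation, the protocol article states: "A minimisation algorithm is used to determine participant allocation, using site, gender, age group". Cuff tear size is the fourth factor, and a 70% random element is built in.

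The Statistical analysis plan section defines the primary analysis as an intention-to-treat comparison of 12-month OSS, with test statistics and boundaries taken from a cited methodology paper. If the trial stops early, the deletion method for overrunning applies, with "clinical inferences following directly from widely used methods for unbiased estimates and confidence intervals in group sequential trials". No covariate is named in that paragraph.

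The next paragraph says: "The primary analysis will be augmented by calculating adjusted estimates of treatment group differences (with 95% CIs) for the OSS using a mixed-effects model". That model has a random effect for centre and fixed effects for age, gender and tear size. Estimates for the other outcomes are to follow the same approach.

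Baseline OSS is listed under Secondary outcomes as collected, but neither analysis is said to use it.

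**The concern.** If the primary analysis already adjusted for the minimisation factors, there would be no reason to augment it with adjusted estimates. The natural reading is that the sequential test and its estimate are unadjusted.

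Minimisation forces the arms to be alike on its factors. If those factors predict 12-month OSS, the treatment difference varies less from trial to trial than an unadjusted standard error supposes. The test then rejects less often than its nominal level under the null, and its interval is wider than it needs to be. Baseline OSS is not a minimisation factor, so leaving it out does not disturb the error rate, but any precision it could give is forgone.

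This matters most for the sequential analysis because that is the one that decides whether the trial stops and what it concludes. The more precise analysis has only a supporting role.

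**Working it through.** **Inputs from the article (Power and sample size).** Target difference and SD: "estimated the target difference for the OSS as 6 and an SD of 12 has been observed in multiple studies". Two-sided 5%, 90% power. Adaptive design: "188 participants would be sufficient to detect a 6 point difference in OSS between treatment arms with 90% power", which is 94 per arm.

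**The plan's own figures.**
- Fixed design: n per arm = 2(1.960 + 1.282)² × 12² / 6² = 84.06, rounded up to 85, so 170 in total. This matches "assuming an approximate normal distribution for the score data, would require 170 participants".
- Loss to follow-up: 188 / 0.85 = 221.2, against "Allowing for 15% lost to follow-up, while striving to keep this below 10%, gives a maximum study sample size of 221". This agrees apart from rounding.
- The 188 comes from simulation with confidential boundaries and cannot be reproduced here; 188/170 = 1.106.

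**Assumption.** The documents give no figure for how much outcome variance the minimisation factors explain. Call it R² and take 5%, 10% and 20%. Assume allocation balances the factors almost perfectly.

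**Actual two-sided level of the unadjusted test.** The true standard error is √(1 − R²) times the one used, so the level is 2[1 − Φ(1.96/√(1 − R²))].
- R² 5%: 1.96/0.975 = 2.011, level 4.4%.
- R² 10%: 1.96/0.949 = 2.066, level 3.9%.
- R² 20%: 1.96/0.894 = 2.191, level 2.8%.

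**Power at 94 per arm, treated as a fixed design.** Unadjusted standard error = 12√(2/94) = 1.750, so 6/1.750 = 3.428. With R² = 0, power = Φ(3.428 − 1.96) = 92.9%. Otherwise:
- unadjusted: Φ[(3.428 − 1.96)/√(1 − R²)]
- adjusted: Φ[3.428/√(1 − R²) − 1.96]

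| R² | Unadjusted | Adjusted | Difference (points) | Interval width, adjusted/unadjusted |
|---|---|---|---|---|
| 5% | Φ(1.506) = 93.4% | Φ(1.557) = 94.0% | 0.6 | 0.975 |
| 10% | Φ(1.547) = 93.9% | Φ(1.653) = 95.1% | 1.2 | 0.949 |
| 20% | Φ(1.641) = 95.0% | Φ(1.872) = 96.9% | 2.0 | 0.894 |

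**Imperfect balance.** Simulating the stated 70% rule with 188 participants and an assumed 24 sites gave unadjusted levels of 5.1%, 4.3% and 3.3% at R² 5%, 10% and 20% (3,000 trials each). A separate run gave 4.9%, 3.9% and 3.6% (4,000 trials each). The direction is the same, but the loss is smaller than the formula gives: nothing visible at 5%, and a clear effect only towards 20%.

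**Baseline OSS.** The level formula does not apply, because allocation does not balance it. Unadjusted power stays at 92.9% whatever it explains. Adjusting for a baseline score that explained 10% of variance would raise power to 95.1%, by the adjusted formula above.

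**The case against.** The strongest reply is that an unadjusted primary test with an adjusted supporting model is a legitimate choice. The hierarchy is stated: one analysis is primary and the other augments it. The sample size rests on the total SD of 12, so the unadjusted test already delivers the planned power, and the gain from adjusting is at most about 2 points over the R² range used here. The test statistic is defined in a paper that is not at hand, so its being unadjusted is an inference. All of this stands. It limits the size of the point, but it does not give a reason to leave known design factors and a collected baseline score out of the decisive analysis.

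A reader might infer three stronger things that the documents do not support.

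- *That type I error is inflated or the trial is underpowered.* The error is in the conservative direction, and every power figure in the table is above 90%.
- *That the supplementary adjusted estimate carries an ordinary interval which ignores the stopping rule.* The article says only that 95% intervals will be given. It names no type, and the SAP and adaptive charter are not shown.
- *That such an interval would seriously mislead.* If it were ordinary, simulation under assumed boundaries gives overall coverage of about 94% to 95% and average bias of at most about 0.25 OSS point once already recruited participants are followed up and included, as the planned overrunning analysis does. Without overrun, coverage fell to about 91% and bias reached about 1 point in the least favourable scenarios. Worse figures can be produced by conditioning on the reason for stopping, but standard group-sequential intervals aim at unconditional coverage and would not repair those.

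**Conclusion.** The point holds as one of efficiency and consistency with the design. The article implies that the decision-making analysis omits the minimisation factors and baseline OSS. The consequence is modest: a two-sided level of about 4.4% to 2.8% in place of 5%, and 0.6 to 2.0 points of fixed-design power forgone, for R² from 5% to 20%.

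These figures rest on assumed R² values, near-perfect balance and a fixed-design approximation to a sequential test whose boundaries are confidential. With the actual 70% rule the conservatism is likely to be smaller. Whether the supplementary interval reflects the stopping rule is unstated and deserves one clarifying sentence; its overall consequences are close to nominal.

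**What to change.** In the SAP and the adaptive charter, before any formal analysis, define the sequential test statistic from the covariate-adjusted treatment effect on 12-month OSS, with the four minimisation factors and baseline OSS as covariates. Take the information level from the same adjusted estimate. Compare its Z-value with the existing boundaries, and derive the reported group-sequential estimate and confidence interval from it. One adjusted estimate is then primary, and the unadjusted comparison can be kept as a sensitivity analysis.

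If the sponsor prefers to keep the unadjusted primary analysis, the plan should say so openly, acknowledge the conservatism, and state whether the supplementary adjusted interval takes account of early stopping.

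The cost is wording, some programming, and a re-check of information levels and of the design simulations with the adjusted estimator. The Z-scale boundaries and the recruitment target need not change.

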#### Secondary outcomes

The OSS at baseline, 3, 6 and 24 months.The Constant Score at baseline, 3, 6 and 12 months. A standardised protocol for the objective component of the score has been developed based on the work of Moeller *et al* with training provided for all sites.^45–47^
Range of pain-free movement of the shoulder at baseline, 3, 6 and 12 months measured using a long-arm goniometer (12 ½”).Strength of shoulder abduction and flexion at baseline, 3, 6 and 12 months measured using a supplied IsoForceControl EVO_2_ dynamometer (Herkules Kunstoff, Switzerland).Western Ontario Rotator Cuff (WORC) index at baseline, 3, 6, 12 and 24 months.^48^
Health utility assessed using 5-level EuroQol 5 dimension score (EQ-5D-5L) at baseline, 3, 6, 12 and 24 months.^49 50^
Healthcare resource collected at 3, 6 and 12 months.Patient Global Impression of Change (PGIC) score, collected at 3, 6, 12 and 24 months. A simple 7-point scale assessing perception of improvement.^51^
Analgesia use (drug and approximate frequency) collected at baseline and 3, 6 and 12 months.MRI Scans (substudy of 56 patients, 6 weeks and 6 months postsurgery): see the ‘MRI substudy’ section.AEs will be collected from site reports as they occur throughout the first 12 months, and from participants in the 3, 6 and 12 months questionnaires.

Patient-reported outcome measures (OSS, WORC, EQ-5D-5L, PGIC) will be collected at 24 months as a secondary outcome, these will be published separately and will not delay publication of the primary 12-month outcome data. A detailed data management plan has been prepared following Warwick SOPs and will be available on request.

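### The supporting adjusted model for 12-month OSS leaves out baseline OSS; adding it is a free gain in precision and does not touch the primary test

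*Protocol article*

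**What the plan says.** The section Statistical analysis plan of the protocol article makes a group sequential comparison of 12-month OSS the primary analysis, using the test statistics and boundaries of a cited methods paper. It then adds a mixed-effects model to give adjusted treatment differences with 95% confidence intervals. The terms of that model are named: a random effect for recruiting centre and "fixed effects for the variables of interest included in the minimisation algorithm, patient age, gender and size of tear". Baseline OSS is not among them.

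The same section extends the approach: "Estimates of efficacy for the other outcome measures will follow this approach to analysis". The subgroup analyses use the same mixed model with interaction terms added, and are declared exploratory.

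Under Secondary outcomes the schedule includes "The OSS at baseline, 3, 6 and 24 months". Baseline measurements are also listed there for the Constant score, range of movement, strength, WORC and EQ-5D-5L. The minimisation factors under Randomisation are site, gender, age group and tear size, so baseline OSS is not balanced by design. For baseline data, the analysis section states only a descriptive comparison of the arms.

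**The concern.** Baseline OSS is the pre-treatment value of the primary outcome. It is collected before allocation: the section on screening and withdrawals keeps baseline data on people found ineligible during surgery, and randomisation takes place in theatre after that check. Treatment cannot have affected it, so it is a legitimate covariate.

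The article states the model's terms and gives their rationale, namely that they were used in minimisation. An analysis plan that followed this text literally would leave baseline OSS out. Confidence intervals for the adjusted OSS difference, for those secondary outcomes that have a baseline, and for the subgroup interactions would then be wider than the planned data allow. A chance difference in baseline OSS between the arms would be described but not corrected. Adding the covariate after seeing such a difference would be a data-driven choice, which prespecification avoids.

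**Working it through.** **Inputs from the section Power and sample size, and from Randomisation**
- Target difference and SD: "Anchor-based studies have estimated the target difference for the OSS as 6 and an SD of 12 has been observed in multiple studies".
- Error rates: 90% power, 5% two-sided.
- Allocation: "Participants are randomly allocated on a 1:1 basis to the two treatment groups".
- Fixed-design size: "would require 170 participants".
- Adaptive design: the simulations "indicated that 188 participants would be sufficient to detect a 6 point difference in OSS between treatment arms", which is 94 per arm with outcome data.
- Loss to follow-up 15%, maximum 221.

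**Input not in the document**
- r, the correlation between baseline and 12-month OSS. The 0.5 in the sample size section covers only 3, 6 and 12 months, all after surgery. A range of 0.2 to 0.6 is used here as an assumption.

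**1. Reproduce the plan's own figures.** n per arm = 2 × (1.960 + 1.282)² × 12² / 6² = 84.1, rounded up to 85, so 170 in total. This agrees with the article. 188 / (1 − 0.15) = 221.2, against 221 stated. Both reproduce without any baseline adjustment. The 188 comes from simulation with confidential boundaries and cannot be recomputed.

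**2. Reference precision, unadjusted, 94 per arm.** SE = 12 × √(2/94) = 1.75 points. Half-width of the 95% CI = 1.96 × 1.75 = 3.43 points.

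**3. Effect of adjusting for baseline.** The residual SD becomes 12 × √(1 − r²), so the variance falls by r² and the half-width is 3.43 × √(1 − r²).

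| Assumed r | Variance reduction | SE | 95% CI half-width |
|---|---|---|---|
| none (unadjusted) | – | 1.75 | 3.43 |
| 0.2 | 4% | 1.72 | 3.36 |
| 0.3 | 9% | 1.67 | 3.27 |
| 0.4 | 16% | 1.60 | 3.14 |
| 0.5 | 25% | 1.52 | 2.97 |
| 0.6 | 36% | 1.40 | 2.74 |

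**4. Effect of a chance imbalance.** Assume the baseline SD is also 12. The difference in mean baseline OSS between arms then has a standard error of 1.75 points. An imbalance of that size moves the unadjusted estimate by r × 1.75: 0.2 × 1.75 = 0.35 points, 0.5 × 1.75 = 0.88 and 0.6 × 1.75 = 1.05, against a target difference of 6.

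**5. Limit of the comparison.** The reference in step 2 is an unadjusted two-group comparison. The model in the article already adjusts for centre, age, gender and tear size. The gain over that model is set by the partial correlation of baseline with 12-month OSS given those terms. It would be smaller than in the table where those terms already carry part of the same information. The document has no figure from which to compute it.

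**The case against.** The strongest objection is that this is a supporting model. The primary inference is the group sequential test. A reader might infer that leaving out baseline OSS costs the trial power, or that adding it would raise power above 90%. The document does not support that: the mixed model only supplements the primary test, so a change to its covariates leaves the test statistic, the boundaries, the 90% power and the sample size as they are. This part of the objection stands in full.

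A reader might also infer bias. Randomisation already makes the estimate without baseline OSS unbiased, and its confidence interval already allows for chance imbalance. Only r times an imbalance carries into the estimate, not the whole of it. This stands too.

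It is tempting to borrow the stated 0.5 correlation for baseline. The article gives it for follow-up times only, so the 25% line in the table is one point in a range and not the plan's own figure. Nor does the article say that baseline OSS will be complete, only that it is scheduled. Not every secondary outcome has a baseline: PGIC, resource use, adverse events and the MRI measures have none listed.

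Finally, a separate analysis plan is to be agreed with the data monitoring committee and could add the covariate. The sentence carrying the approach to other outcomes need not fix an identical covariate list for each, and the subgroup analyses are openly exploratory. These points lower the stakes. They do not remove the point for the OSS model, because its terms are stated positively and baseline OSS is not one of them.

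**Conclusion.** The point holds as a free improvement to a stated specification. It is not an error that threatens the trial's conclusion. The named covariates for the supporting 12-month OSS model omit the baseline value of the same score, which is scheduled and is not balanced by minimisation.

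The loss is in precision and in correction of the realised imbalance. It ranges from small (4% of the variance at r = 0.2) to material (36% at r = 0.6). This rests on an assumed r, an SD of 12, 94 per arm analysed and an unadjusted reference. The imbalance figures also assume a baseline SD of 12. The same kind of loss applies to the secondary outcomes with a baseline if they take the same covariates, and to the exploratory subgroup models. Its size there cannot be given from the document.

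**What to change.** In the section Statistical analysis plan, and in the separate analysis plan, before unblinding:
- add baseline OSS as a prespecified continuous fixed effect in the 12-month OSS mixed model, beside age, gender, tear size and the random centre effect;
- add it likewise to the subgroup interaction models;
- for each secondary outcome with a baseline measurement (Constant score, range of movement, strength, WORC, EQ-5D-5L), add that outcome's own baseline;
- state how missing baseline values are handled; mean imputation would do for a few.

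The primary group sequential test and the sample size stay as they are. The cost is a line or two of wording and one degree of freedom per model. No new data or participants are needed. If r proves low, little is gained, but little is spent.
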